### Sample size

We based the sample size calculation on expected redemptions of statin prescriptions in the two groups. We expected 80% redemption in the ARR group and 60% in the POL group. This would require 2 groups of each 91 patients to obtain an 80% power with 5% significance in a non-clustered study. Due to clustering, and assuming an intra-cluster correlation of 0.1, we estimated a need for a total of 346 patients for 80% power and 5% significance. We included some buffer due to possible drop-outs and ended up with a total of 380 patients expected to be included by a total of 40 practices.

### Statistical methods

We will use descriptive statistics and analyse differences between groups by means of multilevel logistic and linear regression modeling, to account for possible clustering effects. The models will have three nested levels: patient-, GP-, and practice-level. Regression models will be used to test for differences between the POL- and the ARR-arm in patients’ redemption rates and the COMRADE outcomes, patients’ confidence and satisfaction with communication, respectively. Three of the COMRADE items focus on patients’ ease of understanding information, patients’ satisfaction with the information given, and adequacy of information about issues important for the decision, respectively. We will conduct separate analyses on each of these three items. In addition to the explanatory variable information format (POL *versus* ARR) we will include variables which may either be independently associated with the outcome variable or which have been chosen *a priori* from considerations based on expectations and knowledge within the field. These variables include patients’ baseline risk, patients’ history of angina, impaired circulation or hypertension, patients’ marital status, age and gender, GPs’ professional experience (number of years in general practice), GPs’ prior knowledge of the allocated format, GPs’ workload, and an affiliation between patient and GP of more than five years. Missing responses will be excluded from the analyses.

All analyses will be performed in STATA version 11 (STATACorp, College Station, TX, USA)
[44].

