POL	If people with high cholesterol level like you take the medicine, for the rest of their lives they will on average live 8 months longer than if they do not take medicine

Several studies have evaluated these formats in risk communication and how they can be used in the doctor-patient encounter
[12-16]. The choice of format depends on various factors, e.g. whether the format is perceived to be easy to understand; whether it is correctly understood; whether the format meets patients’ information needs; whether patients receive enough information to make optimal decisions
[17,18]; and how understanding of the format may be affected by factors like age, gender, or educational level. By presenting risk in different ways, framing effects may influence how it is perceived
[19]. A body of research demonstrates that even when conveying essentially the same information, patients, doctors and policy-makers are influenced by differences in format, including the specific wording and presentation (e.g. percentages versus natural frequencies)
[15,20]. Pictorial representations seem to be better understood than natural frequencies, and natural frequencies better than percentages
[15]. A Danish study
[13] has indicated that respondents in a survey tend to be more consistent in their decisions when information is presented in terms of ARR rather than RRR or NNT. Absolute risk is often used by GPs when they communicate risk with their patients and discuss cardiovascular prevention. The GPs often make use of the Systematic Coronary Risk Assessment chart (SCORE)
[21] or national modified algorithms
[22-26]. The SCORE algorithm calculates a person’s 10-year statistical risk of fatal cardiovascular disease by means of the absolute risk in percentages, based on the patient’s gender, age, smoking status, systolic blood pressure and total-cholesterol.

The use of POL in effectiveness communication is a relatively new format of risk reduction. A study of osteoporosis interventions
[27] found that lay people seem to understand POL in the sense that they were able to discriminate between different levels of effectiveness when presented in terms of disease-free survival (i.e. “postponement” of hip fracture), but not in terms of NNT. Similar results have been shown in later studies
[14,28,29]. The studies indicate that the formats representing the most comprehensible effectiveness may be ARR and POL. A recent Danish study

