[40-42] the instrument has been forward-translated from English into Danish and back-translated into English, and finally tested for content validity. The remaining items of the questionnaire concern sociodemographic issues (education, household income, marital status), experience with cardiovascular disease in the patient’s family and self-rated health. Ideally, the questionnaire is to be answered immediately after the consultation for the patients to have a clear memory of the consultation. The patients are to return the questionnaire in a prepaid envelope addressed to the research group. Patients who do not return the questionnaire will receive up to two postal reminders.

After patient recruitment has ended, we will ask the GPs to complete a second questionnaire concerning their experiences with using the agreed quantitative effectiveness format they have been allocated when discussing preventive therapies with their patients.

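### Educational level is collected, and named as a possible influence on understanding of a format, but is not among the covariates listed for the COMRADE models (minor)

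*Protocol article*

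**What the plan says.** Four places in the protocol article bear on this.

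- **Background.** Among the considerations in choosing a format, it lists "how understanding of the format may be affected by factors like age, gender, or educational level".
- **Intervention.** The 35-item patient questionnaire holds the COMRADE instrument, and its remaining items cover "sociodemographic issues (education, household income, marital status" and further topics. Education, marital status and the COMRADE scores therefore come from one form.
- **Outcomes and Statistical methods.** Understanding of the risk information is a secondary endpoint measured with COMRADE. Regression models compare the arms on "patients’ redemption rates and the COMRADE outcomes, patients’ confidence and satisfaction with communication, respectively". In addition, "Three of the COMRADE items focus on patients’ ease of understanding information", satisfaction with the information and its adequacy, and each of the three is analysed separately.
- **Statistical methods, covariates.** Variables enter because they may be independently associated with the outcome or were chosen beforehand "from considerations based on expectations and knowledge within the field". The list opens "These variables include patients’ baseline risk" and goes on to "patients’ marital status, age and gender, GPs’ professional experience" and further GP variables. Education and household income are not in it, and no reason is given. One list is printed for the redemption and COMRADE models together.

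**The concern.** Education appears to meet the protocol's own rule for choosing covariates. It is named beside age and gender as a possible influence on understanding, and age and gender are in the models. Marital status, which that Background sentence does not mention, is in the models and comes from the same questionnaire.

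What is at stake is modest and confined to secondary outcomes. First, if education predicts the COMRADE scores, leaving it out gives up a little precision. Second, GPs were trained in their allocated format and then invited patients, and the section on strengths and limitations says that selection bias in the inclusion of patients cannot be ruled out. If the arms came to differ by education in that way, a model with education in it would remove part of the resulting distortion.

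**Working it through.** **Text check.** The three factors named in the Background, against the later sections:

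| Factor | Recorded? | In covariate list? |
|---|---|---|
| Age | yes (GP form) | yes |
| Gender | yes (GP form) | yes |
| Educational level | yes (patient questionnaire) | no |
| *For comparison:* marital status, not named there | yes (patient questionnaire) | yes |

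No figure printed in the article depends on this point. The sample size concerns redemption only. It reproduces as 91 per group with continuity correction, and 182 × [1 + (10 − 1) × 0.1] = 345.8, printed as 346, at 10 patients per practice.

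**Precision gain.** Assumed, since the article gives neither: a share p = 0.3-0.4 with higher education, and a shift d = 0.2-0.5 SD in a COMRADE score. Education is treated as a yes/no variable in a linear model.

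Share of variance explained = p(1 − p)d²:
- low end: 0.3 × 0.7 × 0.2² = 0.0084, or 0.8%
- high end: 0.4 × 0.6 × 0.5² = 0.060, or 6%

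Proportional cut in the standard error = 1 − √(1 − share):
- low end: 1 − √0.9916 = 0.004, or 0.4%
- high end: 1 − √0.94 = 0.030, or 3%

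**Chance imbalance, for scale.** Further assumed: 380 patients in the 30 recruited practices (the plan ties 380 to 40 practices, and only questionnaire returners enter these models), and an intra-cluster correlation for education of 0.02-0.10.

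- Cluster size: 380/30 = 12.67, so the design effect is 1 + 11.67 × 0.02 = 1.23 to 1 + 11.67 × 0.10 = 2.17.
- SE of the arm difference in the educated share, √(2p(1 − p)/190 × design effect): √(2 × 0.21/190 × 1.23) = 0.052 to √(2 × 0.24/190 × 2.17) = 0.074.
- Resulting one-SE shift in a COMRADE difference: 0.052 × 0.2 = 0.010 SD to 0.074 × 0.5 = 0.037 SD.
- SE of that COMRADE difference, taking the intra-cluster correlation of 0.1: √(2/190 × 2.17) = 0.151 SD.
- Ratio: 0.010/0.151 = 0.07 to 0.037/0.151 = 0.25 of a standard error.

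This shift is not an addition to the standard error. Under randomisation it is one component of the variation that the standard error already measures, so it must not be read as bias.

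**Differential recruitment.** The article gives no information on recruitment by education, so the size of any such effect cannot be calculated.

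**The case against.** The case for leaving the plan alone is substantial.

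- *The list is not closed.* Its opening verb allows further variables, and education could enter under the stated rule. A fuller plan may already contain it. This stands. A reader might infer that the authors decided to exclude education; the text does not show that, and it gives no rationale to argue with.
- *The Background sentence is soft and narrow.* It says that understanding may be affected, and it concerns understanding of a format, not confidence or satisfaction. This also stands. The argument is strongest for the ease-of-understanding item; for the other two items and the two subscales the reason is consistency. If education changes how one format is understood relative to the other, that is effect modification, which a main-effect covariate does not address.
- *Omission is not confounding.* A reader might infer that leaving education out confounds the comparison because so few practices were randomised. The documents do not support that. Chance imbalance is already in the standard error, and omitting a prognostic variable from a linear model under randomisation costs precision only. Only selective inclusion after allocation could produce bias. The article admits that possibility openly, and one covariate would not cure it.
- *More covariates mean more missing data.* Missing responses are excluded, so blanks on education would drop records. For COMRADE the loss is limited to item non-response, because everyone analysed has returned the questionnaire, and marital status already carries the same kind of cost. For redemption the objection holds: that outcome comes from a prescription database and does not need the questionnaire.

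What remains is that a collected variable, which the protocol itself links to one of its outcomes, is absent from a detailed printed list and could be added almost free of charge.

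**Conclusion.** The point holds as a minor improvement to the COMRADE analyses. Nothing in the article is misstated and no figure changes. On the assumed 30-40% with higher education and a shift of 0.2-0.5 SD, adjustment would reduce the standard error by about 0.4-3%. The second benefit, partial protection against recruitment that differs by education, depends on GP behaviour that the article does not describe and cannot be sized. The precision figure is for a score in a linear model; for single items analysed in another way it is only a guide.

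**What to change.** Before the analysis, add educational level as a prespecified covariate in the COMRADE models: above all for the ease-of-understanding item and, for consistency, for the other two single items and the two subscales.

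Do not add it to the redemption model. The shared list already brings marital status from the questionnaire into that model; education would tie the primary outcome further to questionnaire return.

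The cost is one line in the analysis plan and a few records lost where education was left blank. No new data are needed.

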### Participants

#### GPs

In August 2009 the Regional Council of Southern Denmark, provided us with a list of 328 GPs in 13 municipalities in the Region of Southern Denmark (1.2 million inhabitants). At first we had planned to invite only GPs from two of the municipalities, Kolding and Fredericia (a total of 93 GPs), to obtain the number of practices needed. However, we did not succeed in recruiting enough GPs, and in October 2009 we consequently decided to invite all GPs on the list. We invited GPs to participate in a clinical trial concerning use of quantitative effectiveness formats in risk communication in health prevention consultations (typical consultations at which a GP would review risk factors, levels of risk and potential benefits of lifestyle or pharmacological interventions to manage risk). Subsequently, the project manager ([name]) contacted the GPs by phone and provided further details about the trial. During this phone call, the GPs were briefly informed about practicalities if they accepted to participate.

A total of 30 practices (18 single-handed and 12 partnership practices) were included in the study (Figure 
1).

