### Outcomes

The primary outcome measure is patients’ redemptions of statin prescriptions based on data from Odense University Pharmaco-Epidemiological Database (OPED) during a three-month period after inclusion (the day the patient receives risk information and consents to participate). The three months will allow for time to consider and adopt lifestyle changes before initiating cholesterol-lowering therapy in accordance with Danish guidelines for primary prevention of CVD
[22].

OPED covers all individuals in the Region of Southern Denmark and captures information on redemption of reimbursed drugs. Based on the Anatomical Therapeutic Chemical (ATC) classification
[43], OPED has information on the number of packages and number of Defined Daily Doses (DDDs) dispensed, prescriber identification, and date of prescription.

The secondary endpoints are patients’ understanding of the provided risk information, their perception of involvement, confidence in the decision made, and satisfaction with the communication. Here, we will use the COMRADE instrument
[33-39].

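### The missing-data rule, combined with a questionnaire-only covariate, removes questionnaire non-returners from the adjusted primary analysis although their redemption is available from the prescription register

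*Protocol article*

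**What the plan says.** The primary outcome is statin redemption over three months after inclusion, taken from a register. On its coverage, the Outcomes section says: "OPED covers all individuals in the Region of Southern Denmark and captures information on redemption of reimbursed drugs".

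The Statistical methods section describes the redemption and COMRADE regressions together. To the format variable it adds a single list of covariates, one of which is the patient's marital status. The same paragraph ends: "Missing responses will be excluded from the analyses". It does not restrict this sentence to particular outcomes, and it names no other way of handling missing covariates.

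The Intervention section shows where marital status comes from: "The remaining items of the questionnaire concern sociodemographic issues (education, household income, marital status" (the list continues). The questionnaire is ideally completed straight after the consultation and is returned by post. Non-return is foreseen, since up to two reminders are planned. The GP form described under Patients lists age, gender, systolic blood pressure, total cholesterol and consent, but not marital status.

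**The concern.** A patient who consents but never posts the questionnaire has a register outcome and no marital status. Under the stated rule, or simply by the default behaviour of a regression fitted with that covariate, this patient is left out of the adjusted primary model.

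Two things are at stake. First, patients with a known primary outcome are lost in a trial that already has fewer practices than planned. Second, whether the questionnaire comes back is decided after the patient has received the allocated format. The trial itself hypothesises that the format changes satisfaction and confidence, and these could influence who returns a questionnaire about the consultation. Restricting the primary comparison to returners therefore selects on something that the intervention may affect.

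**Working it through.** **Reproducing the plan's figures (Sample size section).** Inputs: "We expected 80% redemption in the ARR group and 60% in the POL group"; 80% power; 5% significance, taken as two-sided because that reproduces the stated number.

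- Without continuity correction: n = (1.960·√(2·0.7·0.3) + 0.842·√(0.8·0.2 + 0.6·0.4))² / 0.2² = 81.2, so 82 per arm.
- With continuity correction: n_c = (n/4)·(1 + √(1 + 4/(0.2·n)))² = 90.95, so 91 per arm. This is the stated figure: "This would require 2 groups of each 91 patients to obtain an 80% power with 5% significance in a non-clustered study".
- Clustering: design effect 1 + (m − 1)·0.1. With m = 10 it is 1.9, and 182 × 1.9 = 345.8, which gives the stated total of 346. The value m = 10 is not stated; it is implied by 346/182.
- Buffer: the plan "ended up with a total of 380 patients expected to be included by a total of 40 practices". Going from 380 to 346 is a loss of 34/380 = 8.9%.

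**Power after excluding non-returners.** The documents give no return rate, so 10, 20 and 30% non-return are assumptions, spread evenly over practices and arms and unrelated to outcome. For N analysed patients in k practices, the effective number per arm is e = N / (2·(1 + (N/k − 1)·0.1)). Solving the continuity-corrected formula for power gives

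Φ[(0.2·(√e − 5/√e) − 1.960·√0.42) / √0.40].

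Example with N = 380 and k = 30: N/k = 12.67, design effect 2.167, e = 87.7, and power = Φ(0.784) = 78.4%.

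| Assumed non-return | N analysed | Power, 30 practices | Power, 40 practices |
|---|---|---|---|
| 0% | 380 | 78.4% | 85.1% |
| 10% | 342 | 76.2% | 83.0% |
| 20% | 304 | 73.7% | 80.3% |
| 30% | 266 | 70.4% | 76.9% |

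The cost of the exclusion is about 2 points at 10% non-return, 5 at 20% and 8 at 30%. The step from 85.1% to 78.4% comes from recruiting 30 practices instead of 40 and is not part of this point. Without continuity correction the 30-practice column reads 83.0, 81.2, 79.1 and 76.4%.

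**Selection.** If a proportion p redeem, and redeemers and non-redeemers return with probabilities a and b, the rate among returners is p·a / (p·a + (1 − p)·b), and the odds of redemption are multiplied by a/b. All return rates here are assumptions.

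- *Same dependence in both arms.* Planned 80% v 60%, with a = 0.80 and b = 0.60 in each arm. ARR becomes 0.64/0.76 = 84.2% and POL becomes 0.48/0.72 = 66.7%. The risk difference shrinks from 20 to 17.5 points, but the odds ratio is 2.67 before and after, because a/b cancels.
- *Different dependence by arm.* True redemption 70% in both arms, ARR return unrelated to redemption, and POL with a = 0.85 and b = 0.65. POL becomes 0.595/(0.595 + 0.195) = 75.3%, a false difference of 5.3 points. The odds ratio is 0.85/0.65 = 1.31 instead of 1.

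**The case against.** The best defence is the wording. A register redemption is not a response, so the sentence may have been meant for questionnaire answers only. The article also does not say that every listed covariate enters every model, or that the adjusted model is the only primary analysis, and a fuller analysis plan may settle these matters. This stands as a possible intention. It does not remove the point: the list is introduced for both kinds of outcome, the rule carries no limit, and even on the narrow reading a model containing marital status drops patients without it unless another method is named.

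Other parts of the defence succeed:

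- The power loss is modest. The buffer absorbs about 9%, and with 40 practices power would still be 80.3% at 20% non-return.
- A reader might infer that a false treatment effect is to be expected. The documents do not support that. In a logistic model, bias in the marginal odds ratio needs return to depend on redemption differently in the two arms, and nothing shows that it does. Redemption is counted over three months, so it will often follow the return of the questionnaire and cannot then have caused it. A link would have to run through the patient's reaction to the consultation.
- A reader might add clinical history and length of affiliation with the GP to the covariates that come from the questionnaire. Their source is not stated. Only marital status is documented, and it is enough.
- A reader might call the primary outcome free of missing data. The stated coverage is reimbursed drugs and individuals in the region.
- A reader might extend the rule to say that one unanswered item discards a patient's COMRADE subscale. The article does not say how incomplete subscales are scored.

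**Conclusion.** The point holds. Taken together, the covariate list, the source of marital status and the unrestricted exclusion rule remove consenting non-returners from the adjusted primary analysis, although their redemption can be read from OPED. Avoiding selection on a post-intervention behaviour is the main reason to change this. The bias is a possibility with a plausible route, not a demonstrated consequence, and the 5.3-point example illustrates it under assumed return rates. The power loss is secondary: about 2 to 8 points for assumed non-return of 10 to 30%, given 380 patients, an intra-cluster correlation of 0.1 and the continuity-corrected formula that reproduces the plan's own 91 per arm.

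**What to change.** 1. Limit the exclusion sentence to the questionnaire (COMRADE) outcomes.
2. State that the primary redemption analysis includes every consented patient linked to OPED, in the arm to which the practice was allocated.
3. Adjust that analysis only for covariates recorded independently of the patient questionnaire, such as age, gender and the risk factors on the GP form. Include GP-questionnaire covariates only if they are complete or imputed. GPs were asked to complete that questionnaire, which does not guarantee a reply, and one missing GP form would remove all of that GP's patients.
4. Move marital status, and any other covariate that proves to come from the patient questionnaire, to a supportive model with multiple imputation that respects clustering by practice.

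The cost is a few sentences and modest programming, with no new data. The small downside is that patient-questionnaire covariates leave the primary model.
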